**“Fitbit Facilitated Walking Intervention” conceptual basis and development:**

The Fitbit facilitated walking intervention was developed for patients with LBP, using physical activity guidelines^39, 40^ in order to assist them maintain their usual activities, and to improve their compliance with the prescribed therapeutic exercise. The intervention consists of: 1) Fitbit wearable device, 2) 10,000 Steps website, and 3) progressive walking program.

The Fitbit device will enable participants to monitor their progress in meeting the target number of steps. Further, the Fitbit wearable device will act as a motivational feedback tool providing immediate information on activity levels. The 10,000 Steps website is a non-profit promotion web-based platform that was developed to increase the physical activity level of the general community and it can be connected and synchronised with the Fitbit account. We are using this website to encourage participants to use the Fitbit device, track and monitor the daily steps progress and share it with other participants. Also, it enables the investigator to monitor and track the participants’ progress and keep in contact with them. The website has high levels of usability.^41^

The average steps inactive people walk (for any purpose) is less than 5000 steps per day.^35, 36^ Therefore, for people to adhere to PA guidelines, they need to start a graded walking program which will be progressed by at least 10% each week.

**Participant’s adherence to intervention and motivation:**

1. Participants’ and investigator’s accounts will be connected using the “Fitbit friends” feature, which allows for Fitbit users to share and compare stats with each other for motivation.
2. The data will be synced periodically to the Fitbit account from the wearable Fitbit device. The Fitbit application uses a Bluetooth Low Energy technology to sync with the Fitbit wearable device. Every time the participant opens the application, the data will be synced if the wearable device is nearby. However, if the compute does not have a Bluetooth, the participants will be instructed to plug the wireless sync dongle into the computer.
3. The participants’ data will be monitored by the investigator using the 10,000 Steps website ([www.10000steps.org.au](http://www.10000steps.org.au)).^42^
4. Participants can log in to the Fitbit account and the 10,000 Steps website and track their progress, and contact the investigator via the 10,000 Steps website.
5. The investigator will have the list of participant’s names with their information so that he/she can track the patients’ adherence and progress, and provide feedback by email, text message or telephone call during the treatment period every week.
6. Participants will receive daily motivational messages from the Fitbit wearable device.

Adherence to the walking intervention will be measured using the Fitbit device by assessing the duration of walking, and number of steps attained, and so intensity of walking (walking steps/walking duration).

**Measures**

**Sociodemographic data**

At the initial assessment demographic information including age, gender, employment status, level of education, health condition, body mass index, smoking and LBP history (previous episodes of LBP, previous surgery for LBP and previous LBP treatments received) will be collected.

**STarT Back Screening Tool**

The STarT Back Screening Tool^31^ has been designed to help clinicians categorise participants with LBP into low, medium or high risk according to their risk of chronicity, developing persistent disabling pain. It is composed of 9 questions about distribution of pain, disability, fear, anxiety, pessimistic thoughts, depression and bothersomeness in the last two weeks. Participants will be asked to choose either agree (0 point) or disagree (1 point) for each question except Question 9 which uses Likert scale comprising 5 possible options (Not at all=0, slightly=0, moderately=0, very much=1 and extremely=1). The total score (1-9) and the psychosocial sub score (5-9) will be calculated. A Score ≤3 point (≤3/9) indicates low risk. Scores ≥4 points (≥4/9) but ≤3 points on the psychosocial sub score **(**≤3/5) indicates medium risk. Scores ≥4 points (≥4/9) but ≥4 points on the psychosocial sub score **(**≥4 /5) indicates high risk. Therefore participants with a score above 3 will be eligible to join the study. The STarT Back Screening Tool has been shown to be valid in identifying subgroups of participants with LBP.^31^

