**Eligibility criteria for participants**

Participants will be included in this study if they:

1. are diagnosed by physiotherapist with non-specific LBP;
2. are aged 18 years or over;
3. are categorized as being at medium or high risk of chronicity using STarT Back Screening Tool^31^;
4. are classified as physically inactive (those who engage in less than 150 minutes/week of moderate intensity, or less than 75 minutes/week of vigorous intensity or an equivalent combination of the two intensities of physical activity as determined by International Physical Activity Questionnaire (IPAQ)^32^;
5. are ready and able to participate in physical activity as determined by The Physical Activity Readiness Questionnaire (PAR-Q).^33^ Those deemed not fit to participate in physical activity by the PAR-Q or aged over 69 years, will need a clearance from their medical practitioner before engaging in physical activity;
6. have internet access.

Participants will be excluded if they have any:

1. contraindications to physical exercise (cardiovascular diseases e.g. myocardial infarction, embolism, or uncontrolled diabetes; orthopaedic impairments; balance problems);
2. serious spinal pathologies (e.g. fractures, tumours or inflammatory diseases such as ankylosing spondylitis);
3. neurological compromise (e.g. spinal nerve compromise or cauda equina syndrome);
4. pregnancy.

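### The protocol's STarT Back key for Questions 1-8 runs against its own Question 9 scoring, risk bands and entry rule; applied as printed, it admits every low-risk combination and turns away every true total of 7-9

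*Protocol*

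**What the plan says.** The third inclusion criterion in the protocol (Eligibility criteria for participants) takes people who "are categorized as being at medium or high risk of chronicity using STarT Back Screening Tool". The criterion gives no scoring key. The key is in the Measures part, under STarT Back Screening Tool.

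That section states:

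- Content: "It is composed of 9 questions about distribution of pain, disability, fear, anxiety, pessimistic thoughts, depression and bothersomeness in the last two weeks".
- Questions 1-8: "Participants will be asked to choose either agree (0 point) or disagree (1 point) for each question except Question 9".
- Question 9: "Not at all=0, slightly=0, moderately=0, very much=1 and extremely=1".
- Low risk: "A Score ≤3 point (≤3/9) indicates low risk".
- Medium risk: "Scores ≥4 points (≥4/9) but ≤3 points on the psychosocial sub score".
- High risk: "Scores ≥4 points (≥4/9) but ≥4 points on the psychosocial sub score".
- Entry rule: "Therefore participants with a score above 3 will be eligible to join the study".

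No other section of the protocol restates or corrects the key.

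**The concern.** The bands and the entry rule need a total that rises with risk. Question 9 is scored that way. Questions 1-8 cover problems such as disability, fear, anxiety, pessimistic thoughts and depression, yet the printed key gives 0 for agreeing and 1 for disagreeing. If agreeing means that the problem is present, eight items fall with risk, one rises, and their sum is then read as if all nine rose.

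The score decides entry and defines the population named in the protocol's first objective. If screening staff followed the printed key, the trial would take in people whom it means to leave out and turn away people whom it means to study. No later analysis can recover patients who were excluded at screening.

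**Working it through.** **Inputs.** All come from the STarT Back section: the two scoring keys, the cut-off of 3 on the total, and the psychosocial cut-off of 4 out of 5.

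**Assumption.** Agreeing with one of Questions 1-8 endorses the problem. The item wording is not printed, so this is inferred from the topics, from Question 9 and from the bands.

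**Notation.** Let a be the number of Questions 1-8 agreed with (0 to 8), and b the Question 9 score (0 or 1).

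- Total in the direction of the risk bands (called the true total here): T = a + b.
- Total under the printed key: R = (8 − a) + b.

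There are 9 × 2 = 18 combinations of a and b.

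**Low risk (T ≤ 3): 7 combinations.**

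| b | a | R |
|---|---|---|
| 0 | 0, 1, 2, 3 | 8, 7, 6, 5 |
| 1 | 0, 1, 2 | 9, 8, 7 |

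Every R lies between 5 and 9, so all 7 are admitted.

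**Medium or high risk (T ≥ 4): 18 − 7 = 11 combinations.**

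| b | a | T | R | Entry under printed key |
|---|---|---|---|---|
| 0 | 4 | 4 | 4 | admitted |
| 0 | 5, 6, 7, 8 | 5, 6, 7, 8 | 3, 2, 1, 0 | excluded |
| 1 | 3, 4, 5 | 4, 5, 6 | 6, 5, 4 | admitted |
| 1 | 6, 7, 8 | 7, 8, 9 | 3, 2, 1 | excluded |

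Seven of the 11 are excluded. Every T of 7, 8 or 9 is among them. A T of 5 or 6 is excluded when b = 0 and admitted when b = 1. A T of 4 is always admitted. The patient with the maximum score (a = 8, b = 1) gets R = 1, which the bands call low risk. The patient who disagrees with all eight statements and is not bothered gets R = 8.

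**By risk category.** The medium/high split depends on which items are endorsed, so all 2^9 = 512 answer patterns were enumerated, with the psychosocial sub-score taken as items 5-9.

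| True category | Patterns | Admitted, printed key | Admitted, agree = 1 |
|---|---|---|---|
| Low | 130 | 130 | 0 |
| Medium | 286 | 202 | 286 |
| High | 96 | 50 | 96 |

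**Sub-score.** Let p be the number of items 5-8 agreed with. The true sub-score is p + b and the printed one is (4 − p) + b. True high risk needs p + b ≥ 4, so (p, b) is (4, 0), (3, 1) or (4, 1). The printed sub-scores are then 0, 2 and 1. No truly high-risk patient can be labelled high, and the 50 high-risk patterns still admitted are all labelled medium.

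**Which line is at fault.** Reversing the key for Questions 1-8 alone makes the entry rule select exactly the medium and high categories (last column). The bands, Question 9 and the entry rule can all stay as they are.

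**The case against.** The strongest reply is that this is two swapped labels in a descriptive sentence. The inclusion criterion refers to the published instrument and not to this sentence. The cut-offs, Question 9 and the sub-score denominators all fit together in the direction of risk. The screening form may well be scored properly. That stands as a limit on the consequence: harm is possible but not shown. It does not remove the contradiction, because this is the only key that the protocol prints and the entry rule is drawn from the same section.

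It is also fair that the meaning of agreement is inferred. The inference is strong, but it is an assumption.

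Three stronger readings are tempting and are not supported:

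- A reader might infer that the printed key shuts out the high-risk category as a whole. It does not: 50 of 96 high-risk patterns are still admitted. Complete exclusion holds only for true totals of 7 to 9.
- A reader might take the pattern counts as patient proportions. Answer patterns are not equally common in a clinic, and the protocol gives no distribution.
- A reader might call the bracketed 1-9 after the total score a wrong range, since nine 0/1 items give 0 to 9. The parallel bracket 5-9 after the sub-score cannot be a score range, because the same section caps that sub-score at 5. Both brackets most plausibly denote item numbers. The notation is unclear but need not be an error.

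**Conclusion.** The point holds as an internal contradiction in the instrument that decides entry. As printed, the key for Questions 1-8 opposes Question 9, the risk bands and the entry rule. If it is applied, all 7 low-risk combinations are admitted and 7 of 11 medium- or high-risk combinations are excluded, contrary to the third inclusion criterion.

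This rests on two conditions: that agreeing endorses the problem, and that screening follows the printed key. A reader might infer that the trial has studied, or will study, the wrong population. The documents do not show that, because they do not say how the screening form is scored. The correction should still be made before screening relies on this text, since the rule as written would select the wrong patients.

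**What to change.** In the STarT Back section, score Questions 1-8 as 1 point for agreeing and 0 for disagreeing, so that they match Question 9 and the cut-offs. The bands and the entry rule need no change.

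Check whatever form or calculation is used at screening. The protocol's Data collection and management section names REDCap for disability, pain, depression, fear of movement and pain catastrophising, but not for this tool, so a check of REDCap alone may miss it. Re-score anyone already screened from their item answers.

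Optionally, state that 1-9 and 5-9 are item numbers and give the score ranges as 0-9 and 0-5.

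The cost is one corrected line, one check of the form, and re-scoring of any completed screening questionnaires.

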**Fitbit Flex wearable device**

The physical activity level and average number of walking steps per day for participants in the experimental group will be measured by Fitbit Flex wearable device.^43^ The Fitbit Flex is a wristband activity monitor that contains a tri-axial accelerometer. The data can be uploaded to the Fitbit website which will be synchronized with 10,000 Steps website. This device has been shown to be accurate and valid in measuring physical activity and quantifying steps.^27, 28, 44^

**Walking intervention adherence**

Participants’ adherence to the walking intervention will be determined using the 10,000 Steps Website and Fitbit Flex device during the treatment period (8 weeks).

**Primary outcomes**

**Disability**

Disability will be measured by the modified Oswestry Disability Index (ODI).^45^ The modified ODI is an important tool used by researchers and clinicians in measuring functional disability in participants with LBP. It is a self-administered questionnaire consisting of ten sections designed to evaluate the activities of daily living. Each section contains six statements scored from 0 (minimum difficulty in performing activity) to 5 (maximum difficulty). The total score ranges from 0 (no disability) to 50 (greatest disability). The modified ODI is valid, reliable and responsive to change in disability in participants with LBP.^45, 46^

**Pain**

Pain intensity will be measured by the Visual Analogue Scale (VAS).^47^ The VAS is one of the most commonly used scales in measuring pain intensity, providing a numerical rating ranging from 0 (no pain) to 10 (worst pain). The VAS has been shown to be valid and reliable for assessing pain in participants with LBP.^48^

**Secondary outcomes**

**Habitual physical activity level and walking steps**

Habitual physical activity level and walking steps in both groups will be measured objectively by Axivity AX3 (Newcastle upon Tyne, UK; product website: http://axivity.com/product/ax3) for seven continuous days. The Axivity AX3 is a wristband activity monitor that contains a tri-axial accelerometer. The device is waterproof, small, light and is ideal for collecting longitudinal movement data. This device has been shown to be accurate and valid in measuring walking steps.^49-51^

**Depression**

Depression will be measured by Beck Depression Inventory (BDI).^52^ It is one of the most commonly used psychological tests for assessing the severity of depression. The BDI is a 21-item self-administered questionnaire; each item contains 4 statements ranging from 0 to 3 based on severity of each item. A higher total score (29-63) indicates severe depression. This tool has a good internal consistency and good content validity.^53^

**Pain catastrophising**

Participants’ experience of pain will be measured by Pain Catastrophising Scale (PCS).^54^ The PCS is a 13-item self-administered questionnaire, each item consists of a 5-point scale ranging from 0 (not at all) to 4 (all the time). The PCS has been shown to be reliable and valid.^55, 56^

**Fear of movement**

Fear of movement will be measured by Tampa Scale for Kinesiophobia (TSK).^57^ This tool is widely used in clinical practice to assess the fear of movement resulting from feeling of vulnerability to re-injury in participants with pain. It is a 17-item self-administered questionnaire, with four-point rating scale (1=strongly disagree, 2=disagree, 3=agree and 4=strongly agree). The TSK has a good validity and reliability.^58, 59^

The primary and secondary outcomes measurement tools and time-points are described in **Table 1**.

| Table 1 Outcome measurement tools and time-points | | | |
| --- | --- | --- | --- |
|  | **Outcome** | **Measurement tool** | **Measurement points** |
| *Primary outcomes* | Disability | Oswestry LBP Disability Questionnaire^60^ | Baseline, post-intervention, follow-up (week 26) |
|  | Pain | Visual Analogue Scale^47^ | Baseline, post-intervention, follow-up (week 26) |
| *Secondary outcomes* | Habitual physical activity level + Habitual daily walking steps | Axivity AX3 | Baseline, post-intervention, follow-up (week 26) |
|  | Depression | Beck Depression Inventory II^61^ | Baseline, post-intervention, follow-up (week 26) |
|  | Fear of movement | Tampa Scale for Kinesiophobia^57^ | Baseline, post-intervention, follow-up (week 26) |
|  | Pain catastrophising | Pain Catastrophising Scale^54^ | Baseline, post-intervention, follow-up (week 26) |

**Study timeline**

The duration of the intervention will be 8 weeks. The outcomes will be assessed at baseline (week 0), post intervention (week 9) and post-randomisation (week 26). See **Table 1** for more details about the measurement tools and times

**Safety and adverse events**

Walking programs are generally safe,^62^ however, it is possible that participants may experience some unforeseen problems such as muscle soreness, falls or other injuries. Participants will be closely monitored to keep track of any unwanted effects or any problems. If there are any unwanted effects the program may be stopped and the reasons will be discussed with the treating physiotherapist and investigator. In case of a serious adverse event, participants will be advised to seek immediate medical assistance.

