**Interventions**

**Control Group**

Participants allocated in the control group will receive usual physiotherapy care provided by their treating physiotherapist. Also, they will be given instructions to maintain their usual physical activity level during the treatment period.

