**Experimental Group**

Participants in the experimental group will receive a Fitbit walking intervention provided by the investigators in addition to usual physiotherapy care provided by their treating physiotherapist.

During the baseline period, participants will be requested to wear a physical activity monitor (Axivity AX3 and Fitbit Flex wearable devices) for seven continuous days, to measure the total number of habitual walking steps per week. The baseline average daily walking steps for participants will be calculated by dividing the total number of habitual walking steps per week by seven (total walking steps per week/7). During the intervention each participant’s average daily walking steps will be progressed each week by a minimum 10%. To comply with current physical activity guidelines, participants will be asked to walk the prescribed number of steps at a moderate intensity (i.e. brisk walking, 100 step/min).^35-38^ Participants will be asked to partake in the prescribed walking program at least five days per week for 8 weeks.

Participants in the experimental group will receive a Fitbit Flex wearable device and will attend a training session delivered by the investigator to: 1) install and set up the Fitbit wearable device and account, 2) register the participant in the 10,000 Steps website and synchronise the device with the Fitbit account, and 3) provided with instructions of using the device and account including monitoring step counts as well as other features. Additionally, participants will receive a handbook detailing all of the instructions provided from the training session.

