**Data collection and management**

The subjective data (disability, pain, depression, fear of movement and pain catastrophising) will be collected online using Research Electronic Data Capture (REDCap).^63^ The objective data (habitual physical activity level and daily walking steps) will be collected by Axivity AX3**.**

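### No adverse-event item is named for both groups and weekly investigator contact is described for the experimental group only, so soreness, falls and injuries are likely to be found more often there

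*Protocol*

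**What the plan says.** Safety and adverse events names muscle soreness, falls and other injuries as possible problems and then states: "Participants will be closely monitored to keep track of any unwanted effects or any problems". No question, form, time point or recorder is attached to this. The next sentence is framed around the walking program: "If there are any unwanted effects the program may be stopped".

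Data collection and management lists what is gathered. For questionnaires: "The subjective data (disability, pain, depression, fear of movement and pain catastrophising) will be collected online using Research Electronic Data Capture". For devices: "The objective data (habitual physical activity level and daily walking steps) will be collected by Axivity AX3". Table 1 gives the primary and secondary outcomes at baseline, post-intervention and week 26. None of these places has an adverse-event item.

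On contact during treatment, the section on adherence and motivation (item 5) has the investigator track progress and "provide feedback by email, text message or telephone call during the treatment period every week". Item 4 of that section lets participants reach the investigator through the 10,000 Steps website. Both belong to the walking intervention, and the Experimental Group section says who receives it: "Participants in the experimental group will receive a Fitbit walking intervention provided by the investigators". For the other group the text reads: "Participants allocated in the control group will receive usual physiotherapy care provided by their treating physiotherapist". Controls are also told to keep to their usual activity. No study contact with them is described between baseline and week 9.

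**The concern.** A harms count can be compared between groups only if events are looked for in the same way in each. Here the Protocol commits to tracking unwanted effects but names no shared instrument for doing so. The only scheduled study contact it describes during treatment belongs to one group. A participant in touch with the investigator every week about walking has many occasions to mention a sore leg or a fall. A control participant has no described study channel until the week 9 questionnaires, and those do not ask.

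Two things are at stake. A raw comparison could make the walking program look less safe than it is. Alternatively, events noted in walkers could be left without a control rate to judge them against, although minor soreness and injuries can occur in any group of people with low back pain. No later analysis can repair this, because control events that were never asked about are not in the data.

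**Working it through.** The Protocol states no figure on adverse-event detection, so there is none to reproduce. The check sets the sections side by side and then shows how unequal detection acts.

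**Channels by which an event could reach the study before week 9**

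| Channel | Experimental | Control | Source (Protocol) |
| --- | --- | --- | --- |
| Weekly email, text or call from the investigator | Yes, over 8 weeks, so about 8 | None described | Adherence and motivation, item 5; Control Group |
| Messages to the investigator through the website | Yes | None described | Adherence and motivation, item 4 |
| Treating physiotherapist | Yes, frequency not given | Yes, frequency not given | Control Group; Experimental Group |
| Duty on the physiotherapist to record or report events | Not stated | Not stated | Safety and adverse events |

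**Items collected in both groups at weeks 9 and 26**

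| Item | Would show |
| --- | --- |
| Pain (VAS), disability (ODI) | Sustained worsening, equally in both groups |
| Depression, fear of movement, catastrophising | Not adverse events |
| Axivity activity and steps | Not adverse events |
| Adverse-event item | None named |

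The gap is therefore specific: soreness, falls, other injuries and transient flare-ups.

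**Illustration (all rates assumed)**

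- Group size: 34 per group (Sample size section).
- True event risk r, the same in both groups. Detection probability d_E in the experimental group and d_C in controls.
- Expected observed participants with an event = 34 × r × d.
- Observed risk ratio = (r × d_E)/(r × d_C) = d_E/d_C. The true risk cancels.

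With r = 20% and d_E = 90%, the experimental group shows 34 × 0.20 × 0.90 = 6.1.

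| d_C | Expected in controls | Observed risk ratio |
| --- | --- | --- |
| 90% | 34 × 0.20 × 0.90 = 6.1 | 1.00 |
| 70% | 34 × 0.20 × 0.70 = 4.8 | 0.90/0.70 = 1.29 |
| 50% | 34 × 0.20 × 0.50 = 3.4 | 0.90/0.50 = 1.80 |
| 30% | 34 × 0.20 × 0.30 = 2.0 | 0.90/0.30 = 3.00 |

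The chance of a nominally significant difference (two-sided 5%) in the last three rows is about 7%, 16% and 33% by the normal approximation for two proportions. Counts this small make that approximation rough; Fisher's exact test gives about 4%, 8% and 19%. The likelier consequence is thus a misleading descriptive table rather than a false significant result.

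**The case against.** Several points on the other side stand, and they limit what can be claimed.

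- **The lists are not exhaustive.** Data collection and management leaves out data that are plainly collected elsewhere, such as sociodemographic items and the STarT Back tool, and Table 1 covers declared outcomes only. Their silence does not prove that events go unrecorded. It shows that no common item is named.
- **The monitoring promise is not limited to one group.** The sentence on close monitoring speaks of participants in general. The text around it is about the walking program, so the reading is open, but the sentence supplies no mechanism for either group.
- **Both groups see a physiotherapist.** A reader might infer that the contrast is about eight contacts against none. That holds for described investigator contact only, not for clinical contact through which an event could come to light.
- **The weekly contact is feedback on adherence and progress.** A reader might infer that events will certainly be found more often in walkers. The Protocol does not say that the investigator asks about events, so more frequent detection is likely, not certain.
- **No comparison of harms is a stated objective.** A reader might infer that the trial's planned conclusions are biased. The objectives, outcomes and analysis section make no between-group safety claim. The bias would attach to such a statement if one were made.
- **Sustained worsening has a control rate.** VAS and ODI measure it equally in both groups.
- **The illustrated ratios only restate the assumed detection rates.** They show direction and mechanism, not an estimate.

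Leaving the matter to a statistical analysis plan would not answer it. Such a plan can analyse harms data but cannot create data that were not collected.

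**Conclusion.** The point holds as a weakness in how harms are ascertained. The Protocol promises monitoring, names no adverse-event item common to both groups, and describes scheduled investigator contact and website messaging in one group only. The shared physiotherapy channel carries no stated duty to record or report. On that basis soreness, falls and other injuries are likely to be found more often in the experimental group, and any between-group statement about them could not be read free of ascertainment bias.

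The conclusion rests on one assumption: that regular contact with the investigator raises the chance that an event becomes known. Its size cannot be derived from the Protocol. The primary and secondary outcome comparisons are not touched. This is an inexpensive improvement worth making before recruitment, not a flaw that undermines the trial.

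**What to change.** Add the same short adverse-event items (muscle soreness, fall, other injury, medical visit) to the REDCap questionnaires at week 9 and week 26 in both groups. State that any between-group summary of harms uses these items only. List events learned through the weekly contacts or the website separately, as a description of the experimental group. One added sentence in Safety and adverse events and one in Data collection and management would cover it.

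The cost is a few questions on forms already being sent. There is also a limit: recall runs over 9 weeks at the first form and 26 − 9 = 17 weeks at the second, and walkers who discuss progress weekly may recall more. Identical items reduce differential reporting but do not remove it. The change has to be made prospectively, since events missed in controls cannot be reliably recovered later.
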